### 2.5. Randomization

Participants who meet the inclusion/exclusion criteria and wish to participate in the study will be randomly assigned to either the face-to-face treatment group or TELEA control group. We shall carry out a permutation block randomization (1:1) by generating a set of random numbers where the even numbers define a block of specified ordered random treatment assignments and the odd numbers define the other order of assignment of treatments. The random permuted blocks method should achieve balanced experimental groups. All children from outside the municipality’s constituency (from both groups) will be offered financial help to travel to the hospital.

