## 2. Materials and Methods

A parallel randomized controlled trial with a simple assignment has been designed (1:1) to test the effect of a 12-week specific CRP on respiratory function in pediatric patients with intervened CHDs. The trial will be conducted at the Teresa Herrera Maternal and Child Hospital of the University Hospital Complex of A Coruña (CHUAC) and follow the Consolidated Standards of Reporting Trials (CONSORT) Statement [20]; the treatment protocol is described in accordance with the recommendations of SPIRIT [21].

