#### 2.1.2. Exclusion Criteria

Patients with acute, inflammatory, or infectious health conditions that could pose a risk to them during the program.Patients who have undergone at least one interventional procedure or surgical intervention in a period of no less than 6 months before the start of the study.Lack of cooperation from the child due to immaturity or inability to understand or follow simple instructions required for evaluation or CRP.Lack of motivation from the patient or their guardians.Patients with comorbidities alongside CHDs that may influence exercise capacity or ventilatory function, or prevent participation in the program, such as acute inflammatory or infectious diseases.Withdrawal of informed consent.

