#### 2.2.2. Study Group—Home-Based Cardio-pulmonary Rehabilitation Group

Patients assigned to this group will perform the CRP at their own home. The prescribed physical exercise will be uploaded in video format on the TELEA platform belonging to Galician Health Service (SERGAS). The patients will attend the hospital once at the beginning of the study to learn the program with the physiotherapist, who will tell them what their training heart rate is and the safety ranges in which they should move, and once again at the end of the first month. The program will take place twice a week in their home for 12 weeks. Patients will be encouraged to maintain their habitual activities during the protocol.

Components of the program:Respiratory Physiotherapy Program: Children will use two types of respiratory training with devices—COACH and IMT. The home-based rehabilitation program will follow the same respiratory physiotherapy regimen as the hospital-based group, except for the final phase of incremental resistance in IMT. These children will attend the hospital in person only at the start of and at the end of the first month. They will perform three sets of ten repetitions at 30% of the maximum tested in the first month. Once the first month is over, the maximum will be calculated again, and work will be performed at 60% of this value.

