### 2.4. Sample Size

Since no information has been found on the magnitude of the effect on the topic studied, an effect size of 0.8 has been set, taking into account the scale proposed by Cohen and meta-analysis on the effect of rehabilitation in other respiratory conditions [37]. Sample size calculation was performed for a mean difference analysis of independent groups. The effect size was d = 0.8 alpha level of 0.05, power 80%. The estimated sample size was 26 subjects per group. Considering losses of 10%, the number of subjects needed was 56 subjects. G*Power 3.1 software was used to calculate the sample size.

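### The even/odd rule allows only two block orders, so anyone who knows or infers it and sees earlier allocations can deduce at least half of the assignments

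*Protocol article*

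**What the plan says.** Section 2.5 (Randomization) gives the method: "We shall carry out a permutation block randomization (1:1) by generating a set of random numbers". It then states how the numbers are used: "the even numbers define a block of specified ordered random treatment assignments and the odd numbers define the other order of assignment of treatments". No block length is given. Children are to be "randomly assigned to either the face-to-face treatment group or TELEA control group".

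The arms differ in place of delivery. Section 2.2.1 has supervised group sessions at the hospital twice a week. Of the other arm, section 2.2.2 says: "Patients assigned to this group will perform the CRP at their own home".

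Entry involves judgement. Under section 2.1.1 the paediatric cardiologist assesses each case and decides together with the family and the child. One ground for exclusion in section 2.1.2 is "Lack of motivation from the patient or their guardians".

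The opening of section 2 describes the allocation in other terms: "A parallel randomized controlled trial with a simple assignment has been designed (1:1".

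**The concern.** A permuted-block list protects against prediction because each block is drawn from many possible orders. The rule in section 2.5 draws from two: an even number gives one and an odd number gives the other. Each block therefore contains a single random choice, and everything else in it follows.

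This matters because past allocations cannot be hidden here. The trial runs at one hospital, and staff will see which children attend sessions and which train at home. A clinician who can work out the next arm, and who also judges suitability and motivation, could defer or decline a family without meaning to. A family living far away when the hospital arm is due is an example. The factors involved (distance, motivation, family circumstances) plausibly bear on adherence and outcome. The between-group tests in section 2.6 are unadjusted t or Mann–Whitney tests, which would not correct for such selection.

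**Working it through.** **Inputs**
- Two possible orders per block, 1:1 balance: section 2.5.
- Block length b: not stated, so taken as an assumption over b = 2, 4, 6, 8.
- Number of children: section 2.4 says "The estimated sample size was 26 subjects per group" (52 in total), and 56 after allowing for 10% losses.

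**The plan's own figure.** A two-sided two-sample t test with d = 0.8, alpha 0.05 and power 80% needs 25.52 per group, which rounds up to 26; power at 26 is 0.807. The 26 reproduces. Dividing 52 by 0.9 gives 57.8, so 58 rather than 56. The total is used here only to count blocks, and the difference does not affect the argument. I use 56.

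**Step 1: deducible share under the stated rule.** Take any two different balanced orders of length b. Up to the position where they first differ, both prescribe the same arm, so those assignments are certain. At that position the arm is a coin toss. After it, the order is identified and the rest is certain. So exactly one assignment per block is uncertain:

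deducible share = (b − 1)/b

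| b | Deducible share | Of 56 |
|---|---|---|
| 2 | 1/2 = 50% | 28 |
| 4 | 3/4 = 75% | 42 |
| 6 | 5/6 = 83.3% per complete block | at least 46 |
| 8 | 7/8 = 87.5% | 49 |

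Enumerating every pair of orders for these four lengths gave the same shares. The minimum is 50%, at b = 2.

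**Step 2: correct guesses under the stated rule.** The one uncertain assignment per block is guessed correctly half the time:

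correct guesses = 1 − 1/(2b)

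This is 75% for b = 2, 87.5% for b = 4 and 91.7% for b = 6. Chance alone gives 50%.

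**Step 3: comparison with all permutations.**
- *Blocks of 4 (6 orders).* One third of blocks begin with two of the same arm, which fixes two assignments; the other two thirds fix only the last. Deducible: (1/3 × 2 + 2/3 × 1)/4 = 1.333/4 = 33.3%. Correct guesses by position are 1/2, 2/3, 2/3 and 1, so 2.833/4 = 70.8%.
- *Blocks of 6 (20 orders).* By enumeration, 25% deducible and 68.3% correct guesses.
- *Equal mix of 4 and 6.* Even if each block's size were known, correct guesses would be (4 × 0.708 + 6 × 0.683)/10 = 69.3%, and the deducible share (4 × 0.333 + 6 × 0.25)/10 = 28.3%. Not disclosing the sizes cannot raise either figure.

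**Step 4: if the two orders must be learned.** Suppose the recruiter knows the block length but must discover the two orders from past allocations, with 56 children. In simulation the deducible share averages about 66% for b = 4 and 65% for b = 6. It falls below half in about 2% and 8% of sequences respectively.

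**The case against.** A reader might infer that staff know at least half of the assignments beforehand. The document does not support that. Deduction requires knowing or inferring the rule and following the earlier allocations, and nothing says that recruiting staff have the rule. When the orders have to be learned, even the 50% floor can fail in a small share of sequences.

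The wording of the rule is loose, and the same paragraph speaks of random permuted blocks. The full protocol may describe a richer scheme. This stands as a limit on certainty about the percentages. If it is so, the article's sentence misdescribes the method and still needs correcting.

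The gain also depends on the unknown block length. If blocks are of two, moving to all permutations of four lowers correct guesses only from 75% to about 71%, although the deducible share falls from 50% to 33%. The gain in correct guesses is large only if the two-order blocks are longer.

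It would be wrong to infer that allocation is unconcealed or made before consent. Section 2.5 randomises children who already meet the criteria and wish to take part, and Table 1 puts selection and consent at the first visit. Who holds the list is something an article may leave to the full protocol. Nor does anything show that families have been steered, and the travel help in sections 2.5 and 3.1 partly answers the distance example.

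What remains is the rule itself. It is stated, not omitted, and hiding the list does not cure it, because the next arm follows from the past ones.

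**Conclusion.** The point holds as a conditional one. Under section 2.5 as written, a person who knows or infers the two-order rule and sees earlier allocations can deduce at least 50% of assignments (28 of 56), and 75% (42 of 56) if blocks have length four. All permutations of four would leave 33%.

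This rests on three assumptions:
- the plain reading of the sentence as two orders;
- a block length that the article does not give, so only the lower bound is firm;
- allocations that are visible once made, which is inferred from the hospital and home settings since the article does not use the term open-label.

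The consequence is avoidable exposure to selection bias in a single-centre trial with discretionary entry. No size of bias in any outcome can be derived from the document.

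The description as simple assignment in section 2 is a minor inconsistency of wording. It is not evidence that a different method was used.

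**What to change.** In section 2.5, replace the even/odd sentence with a computer-generated 1:1 list drawn from all permutations of blocks of randomly varying size (for example 4 and 6), with the sizes not disclosed to recruiting staff. Section 3.2 describes the study as under way and section 2.2.1 is partly in the past tense. If enrolment has begun, apply the new list to the remaining allocations; those already made cannot be repaired this way.

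Align the phrase in the opening of section 2 with the block method.

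The cost is a new list and a few words of text, with no extra patients or visits. The downside is a possible final imbalance: stopping midway through a block of 6 leaves the arms at most 3 apart.

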### 2.6. Data Analysis

The normality of the data distribution was analyzed with the test of Kolmogorov–Smirnov. For the descriptive analysis, the mean and standard deviation were used if the distribution of the variables was normal; otherwise, the median and interquartile range were calculated. The qualitative variables of the study will be defined by frequencies and percentages.

Student’s *t* test will be used to compare the intergroup means if the distribution of the variables is normal. The non-parametric Mann–Whitney U test will be applied if the normality of the data is not fulfilled. Levene’s test will be used to test the equality of variances between groups. Welch’s *t*-test will be used if the assumption is not met. Repeated measures t-test or the non-parametric Wilcoxon t-test will be applied for the comparison of intragroup means depending on the normality of the data. The Chi-Square test will be used to test the association between categorical variables.

A confidence level of 95% will be considered for the calculation of the confidence intervals and a significance level of 5% for the statistical tests. The statistical program IBM SPSS Statistics version 28.0.1 will be used to analyze the data.

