#### Outcomes (Table 2)

Assessment of respiratory function/spirometry: Spirometry is the study of choice in pulmonary function laboratories. The parameters it measures are the volume of air that the child breathes in or out in absolute value or related to time; and it is shown in the volume/time curve [33]. It also measures the flow expressed in curves with the flow/volume ratio. The mediations can be simple if slow breathing maneuvers not dependent on time are used or forced if maximum effort is requested in the shortest possible time, thus allowing the study of dynamic volumes and forced flows. The recording will be on a flow/volume curve. The most useful functional parameters obtained after spirometry are forced vital capacity (FVC), forced expiratory volume in the first second (FEV1), maximum expiratory flow (PEF), and the Tiffeneau index FEV1/FVC, FEF25%, FEF50%, FEF75%, FEF25–75%. [34]. The recording is called a spirogram.Classify, based on the results of spirometry, whether the child has restrictive [35], obstructive, or mixed ventilatory pattern:Restrictive pattern: defined as FVC and FEV1 < 80% of the predicted value, with FEV1/FVC > 80% or normal.Obstructive pattern: defined as FEV1/FVC ratio < 70%, FEV < 80%, and normal FVC.Mixed pattern: defined as FEV1 < 80%, FVC < 80%, and FEV1/FVC ratio that may be normal, increased, or decreased.Exercise capacity: Pediatric treadmill ergo-spirometry will be used. This test allows a non-invasive evaluation of the child’s functional capacity by calculating maximum oxygen consumption. It will be performed in our hospital on a treadmill following the Bruce protocol [36]. The Bruce protocol is a diagnostic tool increasingly used in the outpatient follow-up of these patients, in order to obtain an objective evaluation of the exercise capacity of children with CHDs and to know their real physical situation. It also has undeniable value for prescribing an individualized rehabilitation and physical exercise program. Exercise intensity is determined based on heart rate. This will be determined within the transition zone between the first ventilatory threshold (VT1) and the second ventilatory threshold (VT2). The values obtained in ergo-spirometry performed 6 months prior to the start of the intervention program will be used. Within two weeks after completing the cardio-respiratory physiotherapy program, a new test will be performed for comparative analysis.Quality of life: quality of life questionnaires for children and adolescents with heart disease—PedsQL^™^ 4.0 Generic Core Scales and PedsQL™ Cardiac Module 3.0.

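### The between-arm tests do not adjust for the recorded pre values and are chosen by preliminary tests; one pre-specified ANCOVA would be more precise and keep a single estimand

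*Protocol article*

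**What the plan says.** Section 2.6 (Data Analysis) names the between-arm method in full. Normality is checked with Kolmogorov-Smirnov. For Student's t the text reads "test will be used to compare the intergroup means if the distribution of the variables is normal". The Mann-Whitney test "will be applied if the normality of the data is not fulfilled". Levene's test then decides between Student and Welch. No covariate, ANCOVA or mixed model appears. The only tests that explicitly use the pre value are the within-arm paired t and Wilcoxon tests.

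Section 2.4 (Sample Size) is consistent with this: "Sample size calculation was performed for a mean difference analysis of independent groups", with no pre-post correlation.

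A pre value exists. Peak VO2 is an eligibility measurement (section 2.1.1). Table 2 marks ergo-spirometry and every spirometric variable both Pre and Post. The Outcomes section says that, after the programme, "a new test will be performed for comparative analysis".

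**The concern.** Two separate features of section 2.6 cost something.

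First, the baseline is not used as a covariate. A child's own pre value is usually a strong predictor of the post value, and the trial is small and mixed (ages 8 to 17, all types of intervened CHD plus transplant). Blocked allocation as described in section 2.5 balances numbers per arm, not baseline values. Both arms are active and share most of the respiratory regimen, and the Discussion sets the challenge of showing home benefits at least equivalent to those in clinical settings. A narrow interval for the difference between arms is therefore what the trial most needs.

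Second, preliminary tests on the trial data choose the method. Student and Welch compare means; Mann-Whitney compares ranks. Peak VO2 and eight spirometric variables each pass through this switch, so the results could mix mean differences with rank comparisons in a way no one can state in advance.

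The text also leaves open whether the means compared are post values or pre-to-post changes. These two analyses differ in precision, and both fit the wording.

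**Working it through.** **Inputs from the article.** Section 2.4: "The effect size was d = 0.8 alpha level of 0.05, power 80"%; "The estimated sample size was 26 subjects per group". Section 2.6: "a significance level of 5% for the statistical tests"; sidedness is not stated.

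**Assumed.** The pre-post correlation r is not given, so 0.3 to 0.8 is used. Pre and post SDs are taken as equal, and effects are in SD units of the post value.

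**1. The plan's own figure.** Noncentral-t power for two independent means, d = 0.8, two-sided 0.05: 26 per arm gives 80.7% and 25 per arm gives 79.1%. The stated 26 reproduces as an unadjusted two-sided test (one-sided would need 21).

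**2. Variance of the between-arm difference, relative to a post-value t-test.**
- Change-score t-test: 2(1 − r)
- ANCOVA: 1 − r²
- ANCOVA relative to change score: (1 − r²) / [2(1 − r)] = (1 + r)/2

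| r | ANCOVA 1 − r² | Cut vs post value | Change score 2(1 − r) | ANCOVA/change (1 + r)/2 | Cut vs change |
|---|---|---|---|---|---|
| 0.3 | 0.91 | 9% | 1.40 | 0.65 | 35% |
| 0.5 | 0.75 | 25% | 1.00 | 0.75 | 25% |
| 0.7 | 0.51 | 49% | 0.60 | 0.85 | 15% |
| 0.8 | 0.36 | 64% | 0.40 | 0.90 | 10% |

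**3. What this means with 26 per arm.** Noncentrality is (δ/√f)·√(26/2), where f is the variance factor; df is 50 for the t-tests and 49 for ANCOVA. The change-score detectable difference is 0.792 × √[2(1 − r)].

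| r | Detectable at 80% power: post value | Change score | ANCOVA | ANCOVA power at d = 0.8 |
|---|---|---|---|---|
| 0.3 | 0.79 | 0.94 | 0.76 | 84% |
| 0.5 | 0.79 | 0.79 | 0.69 | 90% |
| 0.7 | 0.79 | 0.61 | 0.57 | 98% |
| 0.8 | 0.79 | 0.50 | 0.48 | >99% |

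**4. The price of the covariate.** One degree of freedom. At r = 0 and d = 0.8, power goes from 80.75% to 80.72%, with about 2% expected variance inflation from chance baseline imbalance (1 + 1/48 = 1.02).

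**5. Simulation check of the formulas** (3,000 replicates, true difference 0.5 SD, chosen only as a test value). ANCOVA power was 51%, 70% and 83% at r = 0.5, 0.7 and 0.8, against 53%, 70% and 84% by formula.

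**6. The preliminary tests.** The full chain was simulated with 26 per arm, no true difference and 4,000 replicates per distribution. Kolmogorov-Smirnov was run in each arm with the Lilliefors correction, both pretests at 5%.

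| Data | Type I error, full chain | Welch alone | Sent to Mann-Whitney |
|---|---|---|---|
| Normal | 5.1% | 5.0% | 9% |
| Lognormal (log SD 0.5) | 4.9% | 4.3% | 67% |
| t, 3 df | 4.9% | 4.6% | 52% |

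The error rate is not visibly affected. The choice of estimand is: 9% of truly normal data sets go to a rank test, and skewed or heavy-tailed ones split roughly between the two kinds of test.

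**The case against.** Several stronger readings are tempting, and the article does not support them.

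- **That the baseline is ignored.** A reader might infer this from the absence of a covariate. It is certain only if post values are compared. The wording also fits a change-score test, which does use the baseline, and against that test the gain at r = 0.7 to 0.8 is only 15% to 10%.
- **That the unadjusted comparison is biased or invalid.** It is neither. Allocation is randomised 1:1, and the unadjusted standard error already covers chance imbalance. With 26 per arm that imbalance has a standard error of √(2/26) = 0.28 SD and, at r = 0.7, one such step moves a post-value comparison by 0.7 × 0.28 = 0.19 SD. This is lost precision.
- **That the preliminary tests inflate type I error.** They did not in the three cases simulated.
- **That the gain is large whatever r is.** At r = 0.3 it is 9% against post values. Section 2.1.1 allows a peak VO2 baseline up to 6 months old and admits only children below 80% of predicted; both may lower r for that outcome. If spirometry, recorded in % in Table 2, is analysed as percent of predicted, much of the age-related spread is already removed.
- **That the trial is underpowered for its own target.** At the design effect of 0.8 the planned test has 80.7% power. Whether 0.8 is a sensible target is a different question.

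What stands after these objections: ANCOVA has lower large-sample variance than the post-value test for any nonzero r, and than the change-score test for any r below 1. Section 2.6 states its method rather than deferring it, so this is a choice that can be improved and not a detail left to another document.

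**Conclusion.** The point holds as one of efficiency and of a stable estimand. Section 2.6 fixes a valid but inefficient unadjusted test, leaves post value or change undefined, and lets the data pick means or ranks for each outcome. The size rests on an assumed r and on which unadjusted test would have been run. Against post values the gain is small at r = 0.3 and large from about 0.5 upward; against changes it runs the other way, from 35% at r = 0.3 down to 10% at r = 0.8. For peak VO2 the lower end of r is plausible. The direction of the gain does not depend on r, and the loss if r were zero is negligible. The change should be made, but the planned analysis would not give a wrong answer without it.

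**What to change.** Rewrite the between-arm paragraph of section 2.6. For each continuous outcome with a pre value, analyse the post value by ANCOVA with arm and the outcome's own baseline as covariates, and report the adjusted mean difference with its 95% CI. State one standard error in advance for all outcomes, for example heteroscedasticity-robust, so that no data-dependent choice re-enters. Remove the Kolmogorov-Smirnov and Levene tests as selectors of the method, and keep Mann-Whitney only as a sensitivity analysis. If a t-test is kept instead, say whether it is applied to post values or to changes.

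Cost: wording only. No new data and no change to the sample size are needed, one degree of freedom is spent per model, and ANCOVA is available in the SPSS version named in section 2.6.

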### Main and Secondary Objectives

Main Objectives:To evaluate whether our proposed cardio-pulmonary rehabilitation program improves respiratory function and exercise capacity.To compare outcomes between the hospital-based rehabilitation group and the home-based rehabilitation group.

Secondary Objectives:To identify whether this specific CRP achieves higher adherence rates compared to other programs reported in the literature.To determine if adverse effects occur during or after completing the program.To verify whether the program has been conducted in a safe environment and assess its feasibility in natural settings.To determine if the program leads to improvements in the quality of life of these children and their families.

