#### 2.1.1. Inclusion Criteria

Individual case evaluation will determine eligibility for the Cardiac Rehabilitation Program (CRP). The pediatric cardiologist will assess each case and make decisions in conjunction with the patient’s family and the child or adolescent.

Participant selection will be based on the following criteria:Pediatric patients with a history of cardiac transplantation or CHDs who have undergone at least one interventional procedure or surgical intervention, at least 6 months before the start of the program in a state of clinical stability, hemodynamic stability, and ECG stability (ambulatory patient and does not require inotropic support or other therapies). They should have residual hemodynamic defects of sufficient severity that potentially restrict participation in physical activities, and their perception of fragility may be influenced by the social, family, school environment, or by the patient themselves.Children aged 8–17 years at the start of the study.Present a maximum oxygen consumption figure (peak VO_2_) below 80% of that predicted in ergo-spirometry performed prior to the start of the intervention program (in no case more than 6 months before the start).Patients who do not present contraindications for carrying out the program after evaluation in consultation with a pediatric cardiologist and a rehabilitation doctor.

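### The first main objective, that the program improves function, can be tested only by uncontrolled within-arm pre-post tests, and for peak VO2 these start from the same test that selected the children

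*Protocol article*

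**What the plan says.** All references are to the protocol article.

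- **Objectives** (Main and Secondary Objectives). Two main objectives are listed separately. The first is "To evaluate whether our proposed cardio-pulmonary rehabilitation program improves respiratory function and exercise capacity". The second is "To compare outcomes between the hospital-based rehabilitation group and the home-based rehabilitation group".
- **Arms.** Section 2.2.1 gives the hospital arm the rehabilitation program. Section 2.2.2 says of the home arm: "Patients assigned to this group will perform the CRP at their own home". Section 2.5 has children "randomly assigned to either the face-to-face treatment group or TELEA control group", but this control group is treated. No arm goes without the program.
- **Entry** (section 2.1.1). Peak VO2 must be "below 80% of that predicted in ergo-spirometry performed prior to the start of the intervention program", a test done "in no case more than 6 months before the start".
- **Pre value** (Outcomes). "The values obtained in ergo-spirometry performed 6 months prior to the start of the intervention program will be used". A new test follows within two weeks of the end of the 12-week program. Table 1 puts ergo-spirometry and patient selection together at the first visit and lists no second ergo-spirometry before the program.
- **Tests** (section 2.6). Between arms: Student's t, Welch or Mann-Whitney. Within arms: "Repeated measures t-test or the non-parametric Wilcoxon t-test will be applied for the comparison of intragroup means depending on the normality of the data". The significance level is 5%.
- **Sample size** (section 2.4). It is calculated for independent groups only.
- **Limitations** (section 3.1). Neither the lack of an untreated comparator nor regression to the mean is mentioned.

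**The concern.** Randomisation protects the hospital-versus-home contrast and nothing else. A child's change from before to after the program mixes any program effect with whatever else moves the measurement: calendar time, familiarity with the test, clinical course, growth and measurement error. Without an untreated arm these cannot be separated.

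Peak VO2 has a further problem. A group admitted because one noisy reading fell below a threshold is expected to score higher on retest even if nothing has changed, whenever test-retest reliability is below 1. Here the qualifying reading is also the pre value.

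At stake is the answer to the first-listed main objective. A significant paired test in either arm is the natural evidence for saying that the program improves exercise capacity, and the plan as written gives the reader no other.

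**Working it through.** **1. The plan's own figure.** A two-sided two-sample t-test with d = 0.8, alpha 0.05 and power 80% needs 25.5, so 26 per group, as section 2.4 states. That calculation serves the second objective. No calculation is given for the first.

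**2. Which test can answer objective 1.** Between-arm tests compare hospital with home. If both programs worked equally well, or if neither worked, the expected difference is zero in each case, so these tests cannot show improvement over no program. That leaves the within-arm paired tests.

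**3. Regression to the mean for peak VO2 with no program effect.** The documents give no distribution for peak VO2, so these are assumptions: source-population mean μ = 65 to 85% predicted, SD σ = 15 points, reliability ρ = 0.70 to 0.95, normal values with equal variance on both occasions. From section 2.1.1, the cut-off is 80. From section 2.4, n = 26 per arm.

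Formulas, with φ and Φ the standard normal density and distribution function:
- a = (80 − μ)/σ and λ = φ(a)/Φ(a)
- expected rise = (1 − ρ) σ λ
- variance of the change = (1 − ρ)² σ² (1 − aλ − λ²) + σ² (1 − ρ²)
- chance of a significant rise: noncentral t, 25 df, noncentrality = √26 × rise / SD of change, against the two-sided 5% critical value. The nominal chance in this direction is 2.5%.

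Worked example, μ = 85 and ρ = 0.70: a = −0.333, λ = 1.0215, rise = 0.30 × 15 × 1.0215 = 4.60 points, SD of change 11.0, chance 54%.

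| Source mean | ρ = 0.95 | ρ = 0.90 | ρ = 0.80 | ρ = 0.70 |
|---|---|---|---|---|
| 65 | 0.2 points, 4% | 0.4, 5% | 0.9, 7% | 1.3, 8% |
| 70 | 0.3, 5% | 0.6, 7% | 1.3, 10% | 1.9, 13% |
| 75 | 0.5, 7% | 0.9, 10% | 1.8, 16% | 2.7, 22% |
| 80 | 0.6, 9% | 1.2, 14% | 2.4, 25% | 3.6, 36% |
| 85 | 0.8, 12% | 1.5, 21% | 3.1, 38% | 4.6, 54% |

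Simulation agrees: at mean 85 and ρ = 0.80, 37.6% of 10,000 simulated trials gave a significant rise in one arm.

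**4. Between-arm test under the same conditions.** In that simulation the t-test comparing change between arms rejected in 5.06% of trials against a nominal 5%, because the artefact is the same in both arms.

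**5. Spirometry.** No entry criterion uses FVC, FEV1 or another spirometric value, so step 3 does not carry over. Any drift from time, learning or residual growth still enters the paired test. If the drift has a standardised mean change of 0.1, 0.2 or 0.3 (assumed values), a paired t-test with n = 26 declares improvement in 7%, 16% or 31% of trials.

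**6. Interval between peak VO2 tests.** At most 6 months + 12 weeks + 2 weeks, about 9 months. This is a worst case. Section 2.1.1 makes six months an upper limit, while the Outcomes text reads as a fixed time point.

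**The case against.** The strongest reply is that section 2.6 does not tie tests to objectives. The abstract's aim is comparative, the sample size is for the between-arm comparison, and the article nowhere says that a significant paired test will count as proof of causation. Linking objectives to tests is also often left to a fuller document. It is true that the link is an inference. But objective 1 is stated as a main objective separate from the comparison, the paired tests are listed as significance tests rather than as description, and no further detail in another document could supply an untreated comparator.

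The following limits stand:

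- A reader might infer that regression to the mean affects every outcome. The documents support this for peak VO2 only.
- A reader might infer that a false improvement is likely. The direction is certain for any reliability below 1, but the size rests on outside assumptions. Children with residual defects may come from a source population with a low mean, and the effect is then slight.
- A reader might combine the arms and calculate for 52 children. Section 2.6 specifies within-group tests, so a pooled figure would describe an analysis that is not planned.
- A reader might put much of the change down to growth. Entry is on percent predicted, and Table 2 records spirometry in %. If that means percent of predicted, much of growth is already removed. The unit for oxygen consumption is given only as VO2, so it remains unclear there.
- The two six-month statements can be read as the same rule loosely worded, and Table 1 gives the first visit no date relative to the start of the program.

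**Conclusion.** The point holds. Objective 1 is worded as a causal question, and the design offers only an uncontrolled pre-post comparison to answer it. For peak VO2 the pre value is the selection test, so a significant rise can appear with no program effect: about 0.2 to 4.6 points, and about 4% to 54% of trials per arm of 26 against a nominal 2.5%, under the assumed mean, SD and reliability. For respiratory function the weakness is the missing untreated comparator, not selection.

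A reader might conclude that the trial as a whole is biased. It is not: the hospital-versus-home comparison, the only one that was sized, keeps its error rate. This should still be changed before analysis, because following the stated objective and test could lead to a false claim of improvement.

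**What to change.** 1. Reword objective 1 as a description of the pre-post change in each arm, and make the randomised between-arm comparison the only inferential test.
2. In section 2.6, drop the within-arm significance tests. Report within-arm changes with 95% confidence intervals, without p-values and without attributing them to the program. State that an interval excluding zero is not evidence of a program effect; otherwise the interval simply replaces the p-value, because a paired-t interval excludes zero exactly when p < 0.05.
3. Name the lack of an untreated comparator and regression to the mean in section 3.1.
4. Reconcile the six-month wording in section 2.1.1 with that in the Outcomes text, and record the interval from test to program start for each child.

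Naming the first-visit test as the baseline would not remove the regression, because Table 1 shows that it is the selection test. A repeat test separate from selection would remove that part, but not time, learning or growth.

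The cost of items 1 to 4 is wording and one recorded date interval. The sponsor gives up a causal statement that the program improves function, which this design cannot support.
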